#### Eligibility criteria for hospitals (clusters) and doctors

Hospitals and doctors are eligible for inclusion in the study if: (1) The primary healthcare facilities see at least 100 patients daily. (See sample size calculation); (2) We will recruit doctors from enrolled PHCs willing to participate in the project. To facilitate the arrangement of the investigation schedule, doctors whose daily patient volume is less than 30 or whose clinic hours are irregular will be excluded.

#### Eligibility criteria for patients

In order to cover as many patients as possible, we will enroll patients above the age of 16 and family members accompanying them during their visit. During the study period, these patients will visit the enrolled doctors at least once.

#### Intervention development and description

The interventions adopted in the study are effective in tertiary care hospitals. Implementing scientific assessments identified obstacles and promoting factors, integrating the intervention with routine procedures reduces implementation difficulty, although doctors still experienced an increase in workload, as detailed in the pilot study [41] On this basis, the interventions were adapted and piloted to the characteristics of primary healthcare facilities. First, we conducted semi-structured interviews with doctors in PHCs, revealing that primary care facilities' patient population is predominantly elderly with chronic illnesses and children with common illnesses. Doctors believed that whether patients trust them has the most significant impact on DPC. The lack of patients' health literacy would impair the effect of treatment and undermine doctor-patient trust. Therefore, we adapted the interventions based on these findings to promote DPC in primary care settings.

We then identified feasible implementation methods. Considering physicians' workload and primary healthcare facilities' primary patients, we determined to recruit volunteers to deliver the intervention to patients. During the waiting period, volunteers will engage with patients in the waiting area, provide pre-visit education on the POFHM, and administer a questionnaire after their visit.

### Interventions and control

In China, the relationship between doctors and patients is mainly authoritative [19], and patients lack initiative in the treatment process [42]. This relationship can lead to the consequences of patients not paying attention to self-health management and putting all the blame on doctors [43], which will reduce medical effectiveness and damage doctor-patient trust over time [44, 45]. Therefore, the first good habit of training patients is to activate the patient role, making them realize their essential position and role during treatment.

Even if patients are aware of their role, not all can clearly express their needs [19]. Therefore, it is necessary to train a second good habit of patients to organize their thoughts and identify their most important concerns for their current visit.

The emotional states of doctors and patients inevitably affect communication in the treatment process [46]. Negative emotions can magnify malice, damage the DPR, intensify doctor-patient conflicts, and cause medical disputes [46]. Many studies focus on training healthcare professionals to recognize patients' emotions and provide them with empathetic and supportive care [47, 48]. However, little attention has been paid to patients' role in DPC. Awareness of one's emotions is a prerequisite for controlling them [49]. Therefore, the third good habit of training patients is to be aware of their own and others' emotions. Finally, actively confirming important information with the doctor and remembering medical advice is the fourth good habit that needs to be trained in patients.

Based on the scientific evaluation results of the preliminary trial implementation, it was found that minimal intervention with doctors helps them to better play the supporting role in the research plan [41]. Therefore, this study design will further simplify the FHM interventions for doctors. The four good habits for doctors and patients are detailed in Table 2.

**Table 2 Tab2:** Patient-oriented four habits model (POFHM) intervention description

Habits	Patient (major)	Doctor (minor)
Habit 1: invest in the beginning	Understand the importance of the patient's role	Create rapport quickly
Habit 2: focus on the greatest concern	Sort through the issues of greatest concern	Know what the patient is most concerned about
Habit 3: focus on emotions	Pay attention to emotions	Accept and channel the patient's emotions
Habit 4: invest in the end	Actively summarize information	Summary and feedback

#### Intervention 1: FHM only for patients

The POFHM intervention program for patients consisted of four good habits during visits (see Table 2). The intervention plan was not implemented by making booklets (although we did this in the previous plan) but by recruiting volunteers to ask patients questions to implement the intervention. On the one hand, the potential subjects' visual impairment and limited educational level were considered. On the other hand, hearing a question that requires an answer can better promote patients' thinking, which is the critical point of the intervention design. Below are the detailed implementation points for the four habits.

##### Habit 1: invest in the beginning

The first step of the intervention plan is to activate the patients. We designed four short judgment questions as the first part of the intervention measures. Through questions from volunteers, we encourage patients to reflect on their responsibilities in the treatment process. Volunteers provide straightforward explanations, such as "Seeing a doctor is not only the responsibility of the doctor; patients should also be responsible for their health!", "Doctors cannot cure all diseases like many chronic diseases cannot be cured; doctors can only help you to alleviate or delay the disease " to prompt or deepen the patient's awareness of their role as a patient. The key points of the intervention are (1) patients thinking after hearing the questions and (2) patients recognizing the importance of the " patient's role" after hearing the answers. We do not care about the correctness of the answers.

##### Habit 2: focus on the greatest concern

The second step of the intervention is to help patients sort out their thoughts and identify their most important concerns for this visit. We designed 3–4 short questions as the second part of the intervention. Volunteers delivered the intervention by asking patients questions. The critical point of the intervention is that "patients think after hearing the questions", and we do not care about the specific content of the answers.

##### Habit 3: focus on emotions

In this study, we used the core mindfulness theory to design the intervention's third step. Two simple single-choice questions, such as "Do you have the following feelings now?", "Emotions can be as contagious as a virus"; was used to awaken the patient's awareness of self and others' emotions to make the DPC more harmonious.

##### Habit 4: invest in the end

Based on the initial interview results, we provided the patients with some options for reference, such as retelling, drawing circles, and underlining. While volunteers assign the task to patients, they also emphasize that we will be checking on completing the task.

#### Intervention 2: FHM only for doctors

The researchers will explain the contents of the FHM intervention to the doctors individually and provide complete prompting guidance in writing to intervene with the medical staff. Volunteers are responsible for maintaining order in the waiting room while the patient is waiting and conducting a questionnaire survey after the patient completes the visit. The specific components are shown in Table 2.

#### Intervention 3 (POFHM): FHM both for doctors and patients

The primary focus of the complete POFHM is to cultivate patient visit habits and encourage doctors to provide positive feedback for patients. As we emphasized in the previous section, the construction of the DPR is the result of the joint efforts of both sides. Therefore, the researchers hypothesized that complete POFHM, targeting both doctors and patients, would achieve the best effects.

#### Control group

The essence of the incomplete stepped wedge design is that all primary healthcare facilities entered the study, starting with the control group and then entering different interventions in a randomly assigned sequence for the rest of the study period. During the control period (phase I), the doctors will complete routine consultations according to their habits. Volunteers will be responsible for maintaining order in the waiting room while the patient is waiting and conducting a questionnaire survey after the patient has completed the visit. The written guidance for doctors and the interactive question-and-answer training for patients will only be implemented when they enter the intervention period (phase II and III).

### Primary outcomes

This patient-oriented, physician-supported intervention incorporates the sense of control theory in its design. The intervention focuses on improving patient literacy, with the ultimate goal of effectively improving the quality of DPC.

#### Sense of control

Sense of control will be measured using the 6-item internal health locus of control form A which was developed by Wallston in 1978 [50]. The internal health locus of control form A has been found to have acceptable levels of validity and reliability [51].

#### Patient literacy

Patient literacy will be measured using a patient literacy scale developed by Jiang (2022) [52]. However, the knowledge dimension of the scale was removed because it is not the focus of our attention. Moreover, the items "I will make a doctor's appointment online before my visit" and "When I see the reports of doctor-patient conflicts, I would like to verify" are removed because they do not meet the conditions of the field in a preliminary investigation.

#### Doctor-patient communication

Doctor-patient communication will be measured using 10-item consultation and relational empathy (CARE), which was developed by Mercer et al. in 2004 [53]. The CARE has been widely used in the field of patient-doctor relationships and has demonstrated acceptable levels of validity and reliability [54].

### Sample size

According to our previous work, an absolute increase of 0.13 or more in DPC scores for patients is meaningful. Our sample size of eight clusters (1272 patients) achieves 80% power to detect a 0.13 absolute difference using a two-sided test at the 5% significance level [55, 56]. Our calculation assumes an intra-cluster correlation coefficient of 0.034 [57], an average of 53 patient encounters per site in each 3-day interval. While our study is a cluster RCT, given the cross-sectional nature of a stepped-wedge design and brief intervention period, the effect of individual autocorrelation coefficients (IAC) and cluster autocorrelation coefficients (CAC) on power is negligible, therefore we did not adjust for IAC and CAC [39, 58]. In conclusion, we aim to include 1590 patients to account for a degree of missing data.

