### Statistical analysis

We will use cluster-specific methods because randomization will be performed at the PHC level. For all primary outcomes, an intention-to-treat analysis will be performed. To evaluate the effects of the primary outcomes of the three interventions, generalized linear mixed models will be used, specifying the PHC effect as random and the time effect as fixed [59, 60]. Multiple imputations using chained equations will be used in case of missing data. Subgroup analyses will be conducted to evaluate the interventions' effect in different regions. All analyses will be carried out using Stata 17.0 software. A 2-tailed error rate of 5% will be used to test the hypothesis.

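### Cross-sectional sampling disposes of the individual autocorrelation but not the cluster autocorrelation (CAC), so the power statement and the PHC-only model rest on an unstated CAC of 1

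*Protocol article*

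**What the plan says.** The Sample size section states: "Our sample size of eight clusters (1272 patients) achieves 80% power to detect a 0.13 absolute difference". Testing is two-sided at 5%. The inputs are an ICC ("Our calculation assumes an intra-cluster correlation coefficient of 0.034") and a cell size ("an average of 53 patient encounters per site in each 3-day interval"). On the two autocorrelations it says that "the effect of individual autocorrelation coefficients (IAC) and cluster autocorrelation coefficients (CAC) on power is negligible", and it made no adjustment for either. Its grounds stand in one clause, which offers two reasons: "given the cross-sectional nature of a stepped-wedge design and brief intervention period". It gives no CAC value and no sensitivity range.

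Table 1 describes 8 PHCs in 4 sequences and 7 measurement periods of 3 days within one month, with mostly different patients in each period. The Statistical analysis section specifies a generalized linear mixed model, "specifying the PHC effect as random and the time effect as fixed". It names no PHC-by-period term.

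**The concern.** The two autocorrelations are different quantities. The IAC concerns the same person measured more than once, and fresh patients each period make it irrelevant. The CAC concerns how far a PHC's underlying mean is the same from one period to the next, whoever is sampled. A PHC-specific change in duty rota, case mix or volunteer team between two 3-day windows lowers it in a cross-sectional design just as in a cohort. The first of the plan's two reasons therefore does not reach CAC.

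Two things are at stake. The 80% has no margin, so even a modest PHC-by-period variance takes power below it. The same assumption is also built into the primary model: without a PHC-by-period term, variation of this kind is treated as patient-level noise divided by 53, and standard errors come out too small.

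**Working it through.** **Inputs from the protocol article.** Two-sided alpha 0.05; power 80%; difference 0.13; ICC 0.034; 53 patients per PHC-period; 8 PHCs, 2 per sequence.

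**The plan's own figures.** 8 x 53 x 3 = 1272, so the sample size corresponds to three measured cells per PHC. 1272/0.80 = 1590, the recruitment target. The 80% itself cannot be reproduced, because no SD is given and Fig. 1 is not shown.

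**Size of the neglected variance** (units of SD squared). The sampling variance of a cell mean is (1 - 0.034)/53 = 0.966/53 = 0.0182. A CAC below 1 adds 0.034 x (1 - CAC) to each cell:

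- CAC 0.95: 0.0017, which is 9% of 0.0182
- CAC 0.90: 0.0034, which is 19%
- CAC 0.80: 0.0068, which is 37%

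**Assumed layouts.** Each PHC has one control, one single-party and one combined cell. In the six-period staircase, sequence s is measured in periods s, s+1 and s+2. In the seven-period version it is measured in s, s+1 and s+3. One PHC of each pair receives the patient-only and the other the doctor-only intervention.

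**Method.** Generalized least squares on the 24 cell means with fixed period effects. The covariance between two cells of a PHC is ICC x CAC; the variance of a cell is ICC + (1 - ICC)/53. Total ICC is held at 0.034. The SD is back-solved to give 80% at CAC = 1. For a common effect, SE/SD at CAC = 1 is 0.0950 (six periods) and 0.0913 (seven), so the implied SD is 0.13/(2.802 x 0.0950) = 0.488 and 0.13/(2.802 x 0.0913) = 0.508. If VI is the ratio of the variance to its value at CAC = 1, power is Phi(2.802/sqrt(VI) - 1.960).

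| CAC | VI, six / seven periods | Power, six / seven periods |
|---|---|---|
| 1 | 1.00 / 1.00 | 80% / 80% |
| 0.95 | 1.05 / 1.07 | 78% / 77% |
| 0.90 | 1.10 / 1.14 | 76% / 75% |
| 0.80 | 1.18 / 1.27 | 73% / 70% |

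For example, at CAC 0.90 with six periods: 2.802/sqrt(1.10) - 1.960 = 0.71, and Phi(0.71) = 76%. A staircase with the gap placed directly after the control cell loses less: 78% at 0.90 and 76% at 0.80.

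**Standard error from the PHC-only model, common effect.** The PHC-only fit is taken to assign ICC x CAC to the PHC and the rest to patients. With r the model SE divided by the true SE, actual two-sided error is 2 x Phi(-1.96 r).

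| CAC | r, six / seven periods | Error, six / seven periods |
|---|---|---|
| 0.95 | 0.969 / 0.963 | 5.8% / 5.9% |
| 0.90 | 0.940 / 0.930 | 6.5% / 6.8% |
| 0.80 | 0.890 / 0.874 | 8.1% / 8.7% |

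If the fit instead assigns the full ICC to the PHC, the six-period ratios are 0.975, 0.95 and 0.91, so the table is near the upper end of the shortfall. None of this includes small-sample inflation with 8 clusters.

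**Separate effects**, each contrast anchored at 80% on its own:

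- Patient-only or doctor-only versus control, both given within each sequence: 78%, 76% and 72% at CAC 0.95, 0.90 and 0.80.
- The same contrasts in the six-period staircase when whole sequences alternate between the two: no loss (80% and 82% at CAC 0.80).
- POFHM versus control: 80% (six periods) and 82% (seven periods) at CAC 0.80, so no loss. Under the first variance split the PHC-only SE for this contrast is still 0.93 to 0.95 of the true SE at CAC 0.80.

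**The case against.** The plan gives two reasons, and the second does bear on CAC. With 3-day periods inside one month, PHC means have little time to drift, so a CAC near 1 is plausible. At 0.95 the power loss is only 2 to 3 points. Fixed time effects absorb a calendar shift shared by all PHCs. Unified volunteer training and an on-site research assistant limit team differences. This stands as an argument for a high CAC. It does not show CAC = 1: a 3-day cell also makes PHC-specific rota and case-mix shifts matter more, and the plan neither quantifies nor tests them.

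A reader might infer that power is overstated and standard errors understated as a matter of fact. The documents do not support that: both depend on a CAC they do not give, and the loss is absent for some contrasts and layouts. A reader might also quote error rates of 8-13% from a z-test on the PHC-only model. The plan specifies no z reference distribution, and such a test is liberal with 8 clusters even at CAC = 1 (5.6-8.2% in simulation on two assumed layouts), so those totals mix two problems.

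The target of 1590 gives 1590/24 = 66 per cell. If all were analysed, cell variance at CAC 0.90 would be 0.966/66.25 + 0.0034 = 0.0180, no more than the planned 0.0182. But that surplus is meant to cover missing data, so it is not spare.

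Finally, an article may leave the detailed random-effects structure to an SAP. That lowers the severity of the model point, but the stated reason for dismissing CAC is wrong where it stands.

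**Conclusion.** The concern holds conditionally. The cross-sectional argument does not cover CAC, and brevity supports a high value without establishing 1. If CAC lies between 0.80 and 0.95, the stated 80% for a common effect becomes roughly 70-78%, and the PHC-only model's standard error for that effect is up to about 4% (CAC 0.95) to 13% (CAC 0.80) too small. Single-party contrasts lose similar power or none depending on the layout; POFHM versus control, the intervention expected to work best, loses little or none. The figures rest on assumed CAC values, assumed three-cell layouts and an SD back-solved from the stated 80%. This is a should-fix: the reasoning needs correcting and the model protecting, but nothing shows that the trial is materially underpowered.

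**What to change.** In Sample size, confine the statement of negligible effect to the IAC. State an assumed CAC with its justification, and restate power over a range such as 1.0, 0.95, 0.90 and 0.80, using the actual Fig. 1 layout and the SD behind the 0.13, for each contrast to be tested.

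In Statistical analysis, add a random PHC-by-period effect to the primary model (PHC random, PHC-by-period random, period fixed, three intervention indicators), with a small-sample correction to the degrees of freedom for 8 clusters.

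The cost is one more variance component and a slightly lower stated power, with no extra data. If CAC proves close to 1, little is lost; if not, the primary intervals are protected.

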### Recruitment

We will recruit a convenience sample of practices from Nanling County and West Lake District. We will then arrange an in-person meeting with leaders and family physicians from interested sites to introduce our study and obtain a written agreement from PHCs and doctors. Patients will be recruited when they arrive at these PHCs.

### Randomization and blinding

#### Randomization

Each participating PHC stratified by region will be randomized to one of the predefined timelines (as depicted in Fig. 1) using a single sequence of random assignments. The research assistant will communicate intervention starting times with the participating PHCs.

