## Methods

### Participants

#### Study sites

There were two primary reasons for selecting the implementation site. Firstly, we acknowledged that the economic level and the distinction between urban and rural areas may impact the efficacy of POFHM intervention. Secondly, we aim to verify that the intervention is effective for the majority of Chinese. To ensure that our sample is both representative and universal, we plan to recruit four PHCs in each of our chosen regions, Nanling County and West Lake District in China, which display significant differences. Please refer to Table 1 for an overview of the key components of the stepped wedge design.

**Table 1 Tab1:** Key characteristics of the POFHM trial

Trial characteristics	Definition
Cluster (unit of randomization)	Hospitals or Primary health care facilities (a total of 8)
Number of sequences (steps)	4 (2 hospitals per sequence)
Duration of trial	1 month
Number of measurement periods	7 (length of each period is 3 days)
Individuals	Patients (greater than or equal to 16 years old) visit a doctor at any time during the study
Timing of start of exposure	Patients are exposed to the process when they wait to be seen
Duration of exposure	Patients are exposed for a short period during their visit to the doctor
Measurement	Repeated measurements are from mostly different patients in each period; a tiny proportion of individuals may have repeat visits to the same hospital

The scope of the patient concept in this study extends beyond just the patients themselves and includes their family members and friends

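### Region stratifies the randomisation, but the stated primary model has no region term; the cost is precision, not bias

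*Protocol article*

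**What the plan says.** Under *Study sites* the protocol takes its PHCs from two contrasting places: "we plan to recruit four PHCs in each of our chosen regions, Nanling County and West Lake District in China". It describes them as "Nanling County and West Lake District in China, which display significant differences", and says that economic level and urban or rural setting could change how well the intervention works. Table 1 gives eight clusters, four sequences with two hospitals each, and seven three-day measurement periods.

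Under *Randomization*: "Each participating PHC stratified by region will be randomized to one of the predefined timelines", with the assignments made "using a single sequence of random assignments".

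Under *Statistical analysis* the primary outcomes are analysed by generalized linear mixed models, "specifying the PHC effect as random and the time effect as fixed". Region is not named as a term. It appears only in the next step: "Subgroup analyses will be conducted to evaluate the" interventions' effect in different regions.

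**The concern.** A factor used to stratify the randomisation normally belongs in the primary model, and more so when the trial selected it because the strata differ. Here it is not among the named terms.

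If mean scores differ between Nanling County and West Lake District, that difference becomes part of the random PHC variance. Each PHC appears to contribute only three measured periods, at staggered times. The intervention effects, adjusted for period, therefore draw partly on comparisons between PHCs, and these become noisier as the PHC variance grows. With eight clusters there is little precision to spare.

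The regional question has a related weakness. Whatever method is used, each region supplies four PHCs, and the sample size section covers only the eight-PHC comparison.

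**Working it through.** **Inputs from the protocol.** Eight PHCs, four per region, four sequences (*Study sites*, Table 1). ICC 0.034, 53 patients per PHC per period, 1272 patients, target 1590, difference 0.13, 80% power, two-sided 5% (*Sample size*).

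**The plan's own figures.** 1272 / (8 × 53) = 3, so the total matches three measured periods per PHC. 1272 / 0.80 = 1590, so the target matches a 20% allowance. The 80% power cannot be reproduced, because no SD is given and Fig. 1 is not shown.

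**Assumptions.** Total SD is 1 before any regional difference. The ICC of 0.034 is the PHC share within a region. Each timeline holds one PHC from each region. Regional means differ by d SD, with d = 0, 0.2 or 0.5; the protocol gives no value.

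**Model.** The variance of the fixed effects is (X′Σ⁻¹X)⁻¹, where X holds period and intervention indicators, with or without region. Within a PHC, Σ has σ² + τ² on the diagonal and τ² off it.

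- Cell error: σ² = (1 − 0.034)/53 = 0.01823.
- With region in the model: τ² = 0.034.
- Without it: τ² = 0.034 + d²/4, because each PHC lies d/2 from the overall mean. This is 0.034 at d = 0, 0.044 at d = 0.2 and 0.0965 at d = 0.5.

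**Assumed layouts.** In each, a PHC is measured once under control, once under a single-party intervention and once under the joint intervention.

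- A, six periods: sequence s is measured in periods s, s+1 and s+2; patient-only and doctor-only alternate over sequences.
- B, seven periods: as A, but in periods s, s+2 and s+3.
- C, two start times one period apart, each with one patient-only and one doctor-only sequence.

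**Ratio of SE without region to SE with region** (all ratios are 1.00 at d = 0):

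| Layout | Contrast with control | d = 0.2 | d = 0.5 |
|---|---|---|---|
| A | any intervention | 1.04 | 1.14 |
| A | patient-only / doctor-only / both | 1.09 / 1.10 / 1.10 | 1.49 / 1.54 / 1.50 |
| B | any intervention | 1.05 | 1.20 |
| B | patient-only / doctor-only / both | 1.07 / 1.07 / 1.10 | 1.39 / 1.35 / 1.53 |
| C | any intervention | 1.02 | 1.06 |
| C | patient-only / doctor-only / both | 1.08 / 1.08 / 1.11 | 1.44 / 1.44 / 1.57 |

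**Check that does not need the layout.** With three cells per PHC and region balanced over timelines, the ratio lies between 1 (all information within PHCs) and √[(τ²without + σ²/3)/(τ²with + σ²/3)] (all information between PHCs). With σ²/3 = 0.00608, the ceiling is √(0.05008/0.04008) = 1.12 at d = 0.2 and √(0.10258/0.04008) = 1.60 at d = 0.5. The table respects both.

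**Cost of the extra term.** If inference uses between-cluster degrees of freedom of 8 − 2 = 6, a region term leaves 5. The 97.5% t quantile rises from 2.447 to 2.571, or 2.571/2.447 = 1.05. The term therefore pays for itself only if it shrinks the SE enough to offset about 5%.

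**Regional analysis.** Halving the PHCs doubles the variance. Where eight PHCs give 80% power, four give Φ(2.802/√2 − 1.960) = Φ(0.021), about 51%, for the same effect. A regional difference in effect of that size, taken as the contrast of two separate regional estimates, has Φ(2.802/2 − 1.960) = Φ(−0.559), about 29%. Both use normal quantiles, which is optimistic with so few clusters. Shared period effects could improve the second figure.

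**Randomisation wording.** If one list ignored region, the chance that every timeline received one PHC from each region would be (4! × 4!)/(8!/2⁴) = 576/2520 = 22.9%. Permuting within region gives 100%.

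**The case against.** The analysis paragraph is a condensed summary. It does not spell out the intervention terms either, so it may not be a complete list, and a separate plan may add covariates. This has some force. Still, the sentence does specify the model's structure, and a reader following it would leave region out.

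The gain is also unproven. No regional difference in outcome means is documented; the protocol's stated expectation concerns efficacy. At a small difference, the lost degree of freedom could cancel the benefit. Nor does *Sample size* say whether 0.034 is a within-region figure. All of this stands, and it is why the size is given as a range that starts at zero.

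Three stronger readings are tempting but not supported:

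- **Bias.** A reader might infer that leaving region out distorts the intervention effects. With PHCs balanced by region over timelines, it does not; the random PHC effect absorbs the difference.
- **A contradiction in the randomisation.** A reader might infer that a single sequence of assignments defeats the stratification and confounds region with timeline. The phrase can equally mean one randomisation run, or one list ordered in regional blocks, and either delivers stratification. The 22.9% applies only to a list that ignores region, and the same sentence says the PHCs are stratified.
- **Separate four-PHC models.** A reader might infer that the subgroup analyses are separate fits of 12 cells each. The text neither says this nor excludes an interaction term.

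**Conclusion.** The point holds as a matter of precision. The protocol stratifies by region and presents the regions as different, but its stated primary model has no region term. Omitting it costs nothing if regional means are equal, about 2–11% in SE at a 0.2 SD difference and 6–57% at 0.5 SD. These figures rest on three measured periods per PHC, the assumed layouts, balance of region over timelines, and 0.034 as the within-region ICC. After allowing for the lost degree of freedom, the net effect is roughly neutral around 0.2 SD and favourable in every layout only for larger differences.

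The best reason to make the change is therefore to analyse the trial as it was randomised, with protection if the regions differ as the protocol suggests. Regional effects rest on four PHCs each and can only be exploratory. The randomisation sentence needs clarifying, nothing more.

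**What to change.** 1. In *Statistical analysis*, add region as a fixed effect in the primary model. Cost: one between-cluster degree of freedom and a few words.
2. In the same section, state that regional heterogeneity will be assessed by a region-by-intervention interaction in the joint model with shared period effects. Label it exploratory because each region has only four PHCs, and report regional estimates with intervals. Cost: one sentence.
3. In *Randomization*, state that the four PHCs in each region are randomly permuted over the four timelines, separately by region. Cost: one sentence. If the allocation has already been made, describe how it was done.

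None of this changes recruitment, the interventions or data collection.
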